### Power analysis

2.12

The group size is based on an anticipated increase of cardiorespiratory fitness 2.8 mL/kg/min with a standard deviation of 4.3 mL/kg/min from the previous study.^[16]^ Seventy-six participants will need to be included in the study to achieve 80% statistical power at 5% statistical significance. The drop-out rate in follow-up at 12 week and follow-up is taken into account, that is, 38 participants need to be randomized to the experimental and control arm of the study.

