### Population and randomization

2.2

Participants suitable for this study will be the patients of UH Brno older than 18 years, diagnosed with CHD (angina pectoris or myocardial infraction in last eight weeks), with low or medium cardiovascular risk status (without residual coronary stenosis, value of left ventricular ejection fraction more than 40%).^[17]^ After heart revascularization, the participants will be referred to the II. phase of CR with the recommended pharmacotherapy. Further eligibility criteria will be clinically stable state, ability to perform physical training and cardiopulmonary exercise test (CPET), ability to understand and write in the Czech language, internet connection at home, and literacy with information and communication technology. The participants’ recruitment and allocation will be monitored by the study cardiologist, physiotherapist, or an assistant in UH Brno, Czech Republic.

The exclusion study criteria are patients hospitalized with CHD in the previous 6 weeks, severe psychological or cognitive disorders, serious training limitations besides CHD, participation in another training program under supervision, and contraindications for CPET.

Participants will be randomized (in 1:1 ratio) into the experimental HIIT group and control the MICT group via computer sequence generated by the study statistician. The treatment allocation will be hidden until the completion of the baseline of the initial examinations in sequentially numbered, sealed, opaque envelopes. The study participants cannot be blinded by treatment allocation, but researchers who perform line examinations will be blinded by treatment allocation.

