### Statistics

2.11

The Shapiro-Wilk test will be used to evaluate normality. Comparisons between subjects will be made using the Student *t* test and Mann–Whitney *U* test. The 2-tailed Fisher exact test will test differences in proportions. Data will be summarized as a mean ± standard deviation; *P* values < .05 will be considered statistically significant. Statistica software 12.0 (TIBCO Software Inc, Palo Alto) will be used for statistical analysis.

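### Power analysis: the 38 per arm said to include drop-out equals the two-sided requirement with no drop-out, so 80% power holds only at full retention

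*Protocol article*

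**What the plan says.** Section 2.12 (Power analysis) bases the group size on an "anticipated increase of cardiorespiratory fitness 2.8 mL/kg/min with a standard deviation of 4.3 mL/kg/min", taken from an earlier study. It continues: "Seventy-six participants will need to be included in the study to achieve 80% statistical power at 5% statistical significance". The next sentence reads: "The drop-out rate in follow-up at 12 week and follow-up is taken into account, that is, 38 participants need to be randomized" to each of the two arms.

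The section gives no drop-out rate, no evaluable number separate from the randomised number, and no sidedness.

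Section 2.11 (Statistics) names the Student t test and the Mann–Whitney U test for comparisons between subjects and sets significance at P < .05. The only sidedness stated anywhere is for proportions: "The 2-tailed Fisher exact test will test differences in proportions". Section 2.2 sets 1:1 allocation. Section 2.5 (Outcomes) has cardiorespiratory fitness, the primary outcome, assessed at baseline, 12 weeks and 1 year.

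**The concern.** A sample size that allows for drop-out has two numbers: the evaluable patients needed for the stated power, and a larger number to randomise. Section 2.12 offers 76 as the first and 2 × 38 = 76 as the second. If 76 is already what the power calculation needs, nothing was added for loss, and the sentence about drop-out is not supported by the section's own figures.

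The interpretation of the result is at stake. A reader would take 80% power as robust to loss of patients at 12 weeks and at 1 year. If it is not, a non-significant comparison of HIIT with MICT would be judged against more power than the trial has, most of all at 1 year, well after telemonitored training ends at 3 months. Type I error is not affected by the missing margin.

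**Working it through.** **Inputs.** Difference δ = 2.8 and SD σ = 4.3 mL/kg/min, power 80% and significance 5% (section 2.12); two-sample t test (section 2.11); 1:1 allocation (section 2.2). Assumptions: the 5% is two-sided, and 2.8 is the between-arm difference. Section 2.12 says neither, but these are the conventional choices for a two-arm comparison at P < .05, and together they reproduce 76.

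**Step 1: reproduce the plan's figure.**
- Standardised difference: 2.8 / 4.3 = 0.651.
- Normal approximation: n per arm = 2 × [(1.960 + 0.842) × 4.3 / 2.8]² = 37.02, rounded up to 38. Total 76.
- Noncentral t: n per arm = 38.006. Power at 38 per arm is 79.99%.

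The plan's 38 per arm and 76 in total are therefore reproduced with zero drop-out.

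**Step 2: the margin.** Randomised 38 minus required 38 leaves 0 per arm.

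**Step 3: power when patients are lost.** The t test has 2n − 2 degrees of freedom and noncentrality 2.8 / (4.3 × √(2/n)). The loss rates are assumptions.

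| Evaluable per arm | Loss from 38 | Two-sided power | Difference detectable with 80% power (mL/kg/min) |
|---|---|---|---|
| 38 | 0 | 80.0% | 2.80 |
| 37 | 1 patient | 78.9% | 2.84 |
| 34 | about 10% | 75.4% | 2.97 |
| 32 | about 15% | 72.7% | 3.06 |
| 30 | about 20% | 69.8% | 3.16 |
| 28 | about 25% | 66.7% | 3.28 |

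**Step 4: what an allowance would have looked like.** Inflating 38 by 1/(1 − loss): 38 / 0.90 = 42.2, so 43 per arm (86 in total) at 10% loss; 38 / 0.80 = 47.5, so 48 per arm (96 in total) at 20% loss. Both exceed 76.

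**Step 5: is there another route to 38?** A one-sided 5% t test needs 29.9, so 30 per arm, and 30 / 0.80 = 37.5, so 38. One-sided 5% with 20% drop-out therefore also gives 76. With the 30 per arm left after that loss, one-sided power is 80.2%, but two-sided power at P < .05 is 69.8%.

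**The case against.** The strongest counter-argument is that the two-sided basis is an inference. Section 2.12 states no sidedness, the only two-tailed statement in the article concerns Fisher's test, and the hypothesis is directional (HIIT better than MICT). One-sided 5% with a round 20% drop-out gives 38 per arm and agrees with the sentence that claims an allowance. This stands as a possibility, so the drop-out claim cannot be called false with certainty. It does not rescue the stated power: neither a one-sided test nor a 20% rate appears anywhere, and after that loss a two-sided test at P < .05 would have about 70% power. A calculation for a within-group change would need only 21 patients, but it would not address a comparison between arms.

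It can also be said that the effect is small and that a journal article may leave the drop-out rate to the full protocol. Both are partly right. One patient lost per arm costs about 1 percentage point, and the shortfall becomes material only from about 10% loss. The absence of a rate is not in itself the problem. The problem is that the article asserts an allowance its own figures do not show.

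A reader might go further and infer that the trial never had 80% power. The document does not support that: with all 76 evaluable, power is 80.0%.

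**Conclusion.** The point holds in this form. On the conventional two-sided reading, 38 per arm is the requirement with no drop-out, and the statement that drop-out is included has nothing behind it. The design has 80% power only at full retention; at assumed losses of 10% to 25% the shortfall is about 5 to 13 percentage points.

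This rests on a two-sided 5% t test and on 2.8 being the between-arm difference with SD 4.3. The attrition rates are illustrative. If the calculation was in fact one-sided, the sentence on drop-out could be true, but section 2.12 would still need correcting because 80% would not describe a two-sided P < .05 analysis.

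**What to change.** Revise section 2.12 to state the sidedness of the test, the evaluable number per arm, and the attrition assumed at 12 weeks (T1) and at 1 year (T2). Then:

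- **If the calculation was two-sided:** remove the claim that drop-out is included. Say that 76 randomised gives 80% power only if all are evaluable, and give the power at the assumed attrition (for example about 75% at 10% loss and 70% at 20%).
- **If it was one-sided:** say so, give the drop-out rate used, and report the two-sided power alongside.

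The cost is a few sentences and a less favourable power statement. No extra enrolment is needed for this correction. Adjusting the analysis for baseline peak oxygen uptake may recover some of the power, but the amount depends on a correlation that the article does not give. It should not be promised as a remedy, and it would be a change to the analysis, not only to the wording.

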## Discussion

3

Patients with CHD usually show a significant improvement in cardiorespiratory fitness and health-related quality of life associated with physical training. Improvements in fitness levels have been described in central-based CR programs and, more recently, in home-based settings.^[27,28]^

The traditionally represented method of physical training in studies is MICT. An alternative to MICT in CR has recently been implementing the HIIT training method that provides a more significant improvement in cardiorespiratory fitness values and takes less time, leading to better clinical outcomes in the CHD population.^[29,30]^ On the other hand, the use of the HIIT method at home-based environment can be more difficult and less accurate, as specialists can more precisely adjust the required training intensity in CR clinical centers as needed.

Telemonitoring and telecoaching are also unique and excellent features of telerehabilitation training that facilitate more controlled physical activity. Besides, they allow remote and electronic monitoring of subjects’ compliance with the training, which is a vital and essential characteristic of the approach, which could reliably assess compliance with the training protocol.

Nevertheless, it is crucial to understand this method, which appears to be a better alternative. Scientific proclamation of the American Heart Association recommends focusing on HIIT and assess its impact and safety.^[12]^

The option of telerehabilitation is significant for patients with CHD who cannot (or do not want to) participate in traditional rehabilitation programs. Recent meta-analyze have shown that telerehabilitation technologies are of great importance in preventing CHD, as they can improve the cardiovascular risk factors, functional capacity, and quality of life of those treated remotely.^[31]^ ESC has fully supported the development and expansion of domestic CR.^[32,33]^

This study's conclusion and the main goal will be to fully evaluate HIIT's usefulness as a method of home training in patients with CHD in comparing the effectiveness of the training approach with the results of the traditional MICT protocol. We anticipate that as home-based rehabilitation therapy, HIIT will be superior to standard traditional MICT in improving cardiorespiratory fitness in CHD.

If we show that HIIT significantly increases cardiorespiratory parameters, it means better results in the CHD population, leading to a decrease in mortality and hospital readmission reduction.^[6]^

Secondary analyzes may suggest that even shorter CR programs may lead to better long-term results. If we can prove that telerehabilitation is a safe intervention, it can mean a step towards implementing this method into standard preventive care. The importance of safety and control of home CR remains a challenge, especially as the population of CHD patients ages and the number of comorbidities and the severity of cardiovascular risk increase.^[34]^ The telerehabilitation approach has the potential to positively influence barriers and improve the overall use of the CR program.
